An iterative, theory-guided, design process was used by our group to develop an m-Health BP self-management control program for poor, rurally located Hispanic and African American hypertensive patients called the Smartphone Med Adherence Stops Hypertension: SMASH) [37, 38]. SMASH included multilevel components:Patient-level interventions included: (1) sequential automated reminder signals, (2) tailored Short Message Service (SMS)/voice mail motivational and reinforcement messages based upon adherence to daily medication adherence and BP monitoring (every 3 days); and provider-level interventions entailing: (a) emailed summary reports with stepped care guidelines attached every 2 weeks, (b) phone alerts to clinic nurse navigator when verified out-of-range BP measurements occur. Several 3- and 6-month pilot RCTs were conducted with Hispanics and African Americans with uncontrolled HTN. In each RCT, we observed high acceptability, self-efficacy for following a medical regimen, 95–100 % medication adherence, a mean of 95 % achieving guideline-designated BP control compared to an average of 18 % in standard care (SC) patients and large systolic blood pressure (SBP) reductions (mean: -32 mmHg) [39, 40]. SMASH is capable of adaptation to other poor, undereducated patients with HTN using an iterative patient/provider-centered design approach.

The Phone-based Intervention under Nurse Guidance after Stroke (PINGS) study is fashioned after the SMASH program. The objective of the PINGS study is to test whether a theoretical-model-based, m-Health technology-enabled, multilevel integrated approach is feasible in improving sustained BP control among 60 recent Ghanaian stroke patients within 1 month of their stroke, while building capacity in Ghana for longer-term testing of m-Health technology for chronic disease management in this resource-limited setting. A nurse navigator will be employed in the study design as a task-shifting strategy in the care of chronic diseases in SSA where there is a perennial paucity of neurologists and physicians [41].

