### Control arm/standard of care

Inclusion criteria include owning a cell phone with at least SMS and voice mail. To control for attention exposure, they will receive SMS messages dealing with healthy lifestyle behaviors (smoking, diet, physical activity) but not with medication adherence, hypertension- or stroke-related issues. Messages will be of the same frequency and size as those in the intervention arm. Every 3 days (comparable to those in the intervention arm) they will receive lifestyle messages and if they have a smartphone, the SMS messages will have either PDFs attached or weblinks to a brief video clip or series of charts, information, and so forth. This information will be sent in two messages and requires 3–5 min per message to view or listen to (similar to the BP protocol duration). All four physicians will receive the expert consensus guideline charts. Intervention tactics will cease for both groups after the 3-month trial.

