#### Primary outcome measures

For these measures, generalized linear mixed models (GLMM) will be used to compare the two groups with group as primary independent variable and percent success reaching BP control (or resting BP changes individually) as the primary dependent variable (Table 2) [64]. GLMM allow for missing data, measurement at different times and take into account the effect of clustering, i.e., correlation of repeated measurements within patients clustered within MD (Medical Doctor) provider. Group and time (baseline, 3, 6 and 9 months) will be fixed effects; demographics and secondary outcome measures (e.g., medication adherence via the MPR) will be adjustment covariates. We will assess changes over time via a time-by-intervention interaction term in multivariable models. We will estimate differences (for means or proportions) in ancillary moderator and mediator measures between the two groups via 95 % CIs as appropriate (e.g., self-efficacy, autonomous regulation, and so forth.). We will estimate differences (via 95 % CI) in proportions and average slopes between intervention versus control groups and evaluate linearity of trajectories as input for future RCT analysis strategy. We will estimate percent success reaching BP control for each subject over the trial (baseline, 3, 6 and 9 months), and the within-subject longitudinal trajectories (e.g., slopes), and then summarize as mean longitudinal trajectory within each treatment group (e.g., mean slopes with 95 % CI). Intracluster correlation coefficient (ICC) and variance estimates will be obtained of efficacy outcomes and covariance structure of the longitudinal scores for determination of sample size (and hence adequate power) for a future RCT. Multiple imputation methods will be used for missing end-of-study outcomes. Dropout rate, both selective and differential, is an important issue. If more than 10 % of data are missing, we will add an intermediate evaluation point in a future RCT to provide more data for use in endpoint imputation.

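### The planned comparison of average slopes over months 0 to 9 fits badly a treatment that stops at month 3, and can favour control if the effect largely wanes

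*Protocol article*

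**What the plan says.** The statistical section on the primary outcome opens with the main comparison: "generalized linear mixed models (GLMM) will be used to compare the two groups with group as primary independent variable". Group and time (four visits) are fixed effects, and a time-by-intervention term is planned. The article does not state whether time is categorical.

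Two further sentences bring in slopes:

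- Between arms: "We will estimate differences (via 95 % CI) in proportions and average slopes between intervention versus control groups". Slope is a firm commitment here, not an example. The sentence goes on to say that the authors will "evaluate linearity of trajectories as input for future RCT analysis strategy".
- Within patients: a per-patient percentage of success at the four visits comes first, and the same sentence then adds a second summary: "and the within-subject longitudinal trajectories (e.g., slopes), and then summarize as mean longitudinal trajectory within each treatment group". Slope is offered here as an example, and mean slopes with a 95 % CI are the example of the arm-level summary. No other trajectory summary is named.

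On timing, the section on the control arm says: "Intervention tactics will cease for both groups after the 3-month trial". Both arms are then followed for six more months. The Background states the aim as whether the approach "is feasible in improving sustained BP control among 60 recent Ghanaian stroke patients".

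**The concern.** The active phase fills the first third of the observation period. Entry requires SBP of at least 140 mmHg, so on the systolic criterion everyone starts uncontrolled. If the intervention works, control should rise by month 3 and then hold or fall back. One straight line through months 0, 3, 6 and 9 mixes those two phases, and it rewards late control more than early control. The aim concerns sustained control, but a slope does not separate control at every visit from control at the last visit only.

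At stake are the slope summary itself and the trajectory information that this pilot is meant to hand to a larger trial.

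**Working it through.** The article gives no slope figure and no expected control rates for this trial, so there is nothing of its own to reproduce here.

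**Inputs**
- Visits at months 0, 3, 6 and 9 (Statistical analyses, Primary outcome measures).
- Baseline control = 0 (Inclusion criteria, SBP ≥140 mmHg).
- 30 patients per arm (Proposed sample size).
- 95 % and 18 % control and a mean SBP change of -32 mmHg, from the earlier programme described in the Background and used only as illustration.
- All other rates below are assumptions. So is ordinary least squares as the slope estimator.

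**1. Weights.** Mean time is 4.5, the deviations are -4.5, -1.5, +1.5 and +4.5, and the sum of squares is 20.25 + 2.25 + 2.25 + 20.25 = 45. Deviation divided by 45 gives visit weights of -0.100, -0.033, +0.033 and +0.100 per month. Control at month 3, the end of the active phase, lowers the score.

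**2. Patient level, baseline uncontrolled**

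| Controlled at | Slope per month | % of post-baseline visits controlled |
|---|---|---|
| never | 0 | 0 |
| month 3 only | -0.033 | 33.3 |
| months 3 and 6 | 0 | 66.7 |
| month 9 only | +0.100 | 33.3 |
| months 3, 6 and 9 | +0.100 | 100 |
| months 6 and 9 | +0.133 | 66.7 |

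The ranking of month 3 only below never does not depend on baseline. If a patient counted as controlled at baseline (possible under the and/or wording of Table 2), the slopes are -0.133 and -0.100. Dropping baseline does not help: over months 3, 6 and 9, always controlled and never controlled both have slope 0.

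**3. Arm level.** Let d3, d6 and d9 be intervention minus control in proportion controlled, with equal baselines. Then

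slope difference = (-1.5·d3 + 1.5·d6 + 4.5·d9)/45 = (d6 + 3·d9 - d3)/30.

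It is negative exactly when d3 > d6 + 3·d9.

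| Intervention at 3/6/9 (control 18 % throughout) | d3, d6, d9 | Slope difference per month |
|---|---|---|
| 95/50/20 % | 0.77, 0.32, 0.02 | (0.32 + 0.06 - 0.77)/30 = -0.013 |
| 95/60/35 % | 0.77, 0.42, 0.17 | (0.42 + 0.51 - 0.77)/30 = +0.005 |
| 95/70/50 % | 0.77, 0.52, 0.32 | (0.52 + 0.96 - 0.77)/30 = +0.024 |
| 95/95/95 % | 0.77, 0.77, 0.77 | (0.77 + 2.31 - 0.77)/30 = +0.077 |

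In the first row the average advantage over the three visits is (0.77 + 0.32 + 0.02)/3 = 0.37.

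**4. Chance of a negative sign.** I simulated 20,000 trials with 30 per arm, a latent within-patient correlation of 0.4 (assumed) and no physician clustering. The slope difference was negative in about 86 % of trials for 95/50/20 %, 32 % for 95/60/35 % and 3 % for 95/70/50 %. Varying the correlation from 0 to 0.8 barely moved these figures. For 95/50/20 %, the slope was below -2 standard errors in only about 20 % of trials, while the difference in mean proportion controlled exceeded +2 in over 99 %.

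**5. SBP.** Mean changes of 0, -32, -10 and 0 mmHg (all but -32 assumed) give (48 - 15)/45 = +0.73 mmHg per month. That is an apparent rise, although SBP is at or below baseline at every visit.

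**The case against.** The strongest reply is that the slope is not what the trial rests on. The leading comparison is the mixed model with group, time and their interaction. A difference in proportions is planned in the same clause as the slopes. The per-patient sentence begins with percent success over the visits, which is close to the summary proposed below: with baseline uncontrolled, including it only multiplies the figure by 3/4. An early benefit that waned would show in all of these. A reader might infer that the slope could make the trial as a whole judge the intervention worse than control. The documents do not support that, because no progression rule is attached to the slope.

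The reversal also needs a nearly complete loss of effect by month 9, under rates that are mostly assumed. Full waning is not the only course open: under The intervention, Patient level, some patients may restart components after month 3.

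A reader might also want to argue lost power. That does not carry weight here. The sample size is justified by precision rather than power, and a simulation without physician clustering cannot give this trial's power.

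Finally, the within-patient slope is introduced as an example, and linearity is to be checked.

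All of this limits the reach of the point but does not rescue the slope. The between-arm comparison of average slopes is stated without qualification, and slope is the only trajectory summary named. The linearity check is meant for the future trial; nothing says this trial's summary changes if the check fails.

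**Conclusion.** The point holds for the slope summaries. The negative weight at month 3 and the patient-level rankings are exact for a least-squares slope on these four visits and need no assumed rates. The arm-level reversal is conditional: it occurs in expectation when d3 > d6 + 3·d9, even with the intervention ahead at every visit, and it does not occur with a sustained effect. The illustration of -0.013 per month against a mean advantage of 37 points rests on assumed waning.

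The consequence is a misleading supplementary summary and poor input to the next trial's design. The mixed-model comparison of BP control is not undermined. The change is worth making because the better summaries come from data and a model already planned.

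**What to change.** In the statistical section on the primary outcome, replace the average-slope comparison and the mean slopes with:

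- the between-arm differences at months 3, 6 and 9, with 95 % CIs, from the group-by-time model, stating that time is categorical;
- two prespecified between-arm contrasts: change from 0 to 3 months (effect) and change from 3 to 9 months (maintenance);
- the percentage of post-baseline visits controlled as the per-patient summary. It scores control at month 3 only at 33.3 % against 0 % for never, and control at all three visits at 100 %.

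If a slope is wanted for planning the larger trial, use a two-piece line with a knot at month 3.

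The cost is rewording one paragraph; visits, data and model stay as they are. The drawback is two contrasts to report instead of one slope.

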**Methods:**

This two-arm cluster randomized controlled feasibility pilot trial will involve 60 recent-stroke survivors. Using a computer-generated sequence, patients will be randomly allocated into four clusters of 15 patients each per physician: two clusters in the intervention arm and two in the control arm. Patients in the intervention arm will receive a simple pillbox, a Blue-toothed UA-767Plus BT BP device and smartphone for monitoring and reporting BP measurements and medication intake under nurse guidance for 3 months. Tailored motivational text messages will be delivered based upon levels of adherence to the medication intake. Both groups will be followed up for 6 months to compare BP control at months 3, 6 and 9 as primary outcome measure. Physicians assessing BP control will be blinded to arms into which patients are allocated. Secondary outcome measures will include medication adherence scores and Competence and Autonomous Self-regulation Scale scores. A qualitative study is planned after follow-up to explore the lived experiences of participants in the intervention arm.

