## Methods

### Trial design

This is a two-arm cluster randomized controlled trial involving 60 stroke survivors with the physician as unit of randomization and patients as unit of analysis. Each of the four physicians will be recruited and randomly assigned to the intervention or control group by the statistician (who is not involved in provider or patient recruitment nor data collection) using a computer-generated random sequence. Four groups/clusters of 15 eligible patients will be assigned to either control or intervention arms by the study coordinator after having met study criteria for enrollment (Fig. 1). A cluster randomized trial has been chosen to avoid potential treatment contamination in which physicians might unintentionally provide patients with different degrees of attention or blending of treatment protocols. The checklist for the study protocol is provided as Additional file 1.

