#### Proposed sample size

For this feasibility cluster RCT we will recruit 15 patients per cluster (i.e., physician), 30 patients per group (intervention versus control group) (total *n* = 60). We agree with Kraemer et al. [57] that pilot feasibility studies are deficient in estimating effect size with sufficient accuracy for future study design. To this end we will evaluate the availability of subjects, assess proportions approached/consented, and examine the feasibility of PINGS by evaluating adherence and retention rates. Thus, sample size justification focuses on the precision of estimates rather than the power of statistical tests. We will recruit 30 subjects (15 per physician = cluster) per treatment group based on number of degrees of freedom within each cluster, as suggested by Mead, to obtain reasonable precision for variance estimates [58].

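### An ICC from four physicians is meant to size the next trial, but the stated precision argument supports only the within-physician variance; between physicians there are 2 degrees of freedom

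*Protocol article*

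**What the plan says.** Under Trial design, the article describes a cluster trial "with the physician as unit of randomization and patients as unit of analysis", and adds: "Each of the four physicians will be recruited and randomly assigned to the intervention or control group by the statistician". The abstract's Methods paragraph gives the split: "two clusters in the intervention arm and two in the control arm".

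The section Proposed sample size sets 15 patients per physician, 30 per arm and 60 in all. It rests the number on precision and not on power: the cluster size was chosen "based on number of degrees of freedom within each cluster" and the aim is "to obtain reasonable precision for variance estimates". The same section accepts that pilots estimate effect sizes too poorly to design later studies. It attaches no such caution to the ICC.

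Under Statistical analyses, Primary outcome measures, the article states: "Intracluster correlation coefficient (ICC) and variance estimates will be obtained of efficacy outcomes". That sentence adds the longitudinal covariance structure and gives the purpose: setting the size, and so the power, of a future randomised trial.

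**The concern.** An ICC is built from two variances: between patients of the same physician, and between physicians. Degrees of freedom within clusters bear on the first only. The second depends on how many physicians there are, and there are four.

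The sample size section speaks of variance estimates without saying which component it means. The analysis section then names the ICC and the variances together as inputs to the next trial. Precision is the only rationale given for the 60 patients, so it matters that the argument does not reach the component that drives the size of a cluster trial. At stake is the successor: an ICC estimated near zero by chance would remove the allowance for clustering and leave that trial too small.

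**Working it through.** **Inputs from the protocol article.** Physicians: 4, two per arm (Trial design; abstract). Patients per physician: m = 15 (Proposed sample size). The article states no ICC, so true values from 0.01 to 0.20 are assumed. The check takes a continuous outcome at one visit with full retention.

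**The plan's own figure.** 4 × 15 = 60, or 30 per arm. It reproduces. No numerical precision target is given to check further.

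**Degrees of freedom.** Within physicians: 4 × (15 − 1) = 56. Between physicians within arms: 4 − 2 = 2. The section Allocation and concealment also describes randomising patients, which sits badly with randomising physicians. That is a separate matter, and the count of two physicians per arm is the same either way.

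**Precision of each mean square.** The 95% limits, as multiples of the estimate, are df/χ²(0.975) and df/χ²(0.025).
- Within physicians, 56 df: 0.71 to 1.50. This mean square estimates the within-physician variance directly.
- Between physicians, 2 df: 0.27 to 39.5. This mean square estimates the within-physician variance plus 15 times the between-physician variance.

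**Chance of a zero or negative ICC estimate.** The ANOVA estimate is (F − 1)/(F + 14). The ratio of expected mean squares is R = 1 + 15ρ/(1 − ρ), and F/R follows an F distribution with (2, 56) df. The estimate is at or below zero when F ≤ 1. With 2 numerator df the probability has a closed form: 1 − (1 + 1/(28R))^(−28).

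**95% interval for the ICC**, with F set equal to R: (F/q − 1)/(F/q + 14), where q is the 0.975 quantile of F(2, 56) for the lower limit (3.94) and the 0.025 quantile for the upper (0.0253). At ρ = 0.05, R = 1 + 0.75/0.95 = 1.79. The lower limit is −0.04, truncated to 0; the upper is 0.82.

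| Assumed true ICC | R | Estimate ≤ 0 | 95% interval (truncated at 0) |
|---|---|---|---|
| 0.01 | 1.15 | 57% | 0 to 0.75 |
| 0.02 | 1.31 | 53% | 0 to 0.77 |
| 0.05 | 1.79 | 42% | 0 to 0.82 |
| 0.10 | 2.67 | 31% | 0 to 0.87 |
| 0.20 | 4.75 | 19% | 0.01 to 0.93 |

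The mean of F is slightly above R (1.79 × 56/54 = 1.86 at ρ = 0.05). Using it moves the upper limit only from 0.823 to 0.828.

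**Sensitivity.** Ignoring arm gives 3 df but mixes any treatment effect into the ICC. Even then the upper limit at 0.05 is 0.62. An observed ICC of exactly zero would still have an upper limit of 0.72. With 150 patients per physician a zero estimate at true ICC 0.05 becomes rarer (11%), but the df stay at 2 and the interval still runs from 0.01 to 0.70.

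**Consequence for a successor**, assuming that it also has 15 patients per physician and takes a zero estimate at face value. The design effect needed is 1 + 14ρ, the one used is 1, and the shortfall is 1 − 1/(1 + 14ρ):
- ρ = 0.01: 1 − 1/1.14 = 12%
- ρ = 0.02: 1 − 1/1.28 = 22%
- ρ = 0.05: 1 − 1/1.70 = 41%

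**The case against.** The best defence is that the article never says the ICC, or the between-physician variance, will be precise. Its stated basis is openly within-cluster, and the two statements stand in different sections. That is right as far as it goes. But the precision claim is not limited to one component, and the analysis section pairs the ICC with the variances for the same use.

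A second defence is that nothing says the pilot's point estimate will be the only input. A reader might infer that the successor will be sized on that figure alone; the documents do not say so, and that trial will have its own protocol. Details such as an interval or outside ICC values may also stand in a fuller document. The shortfalls above are therefore conditional. What remains is a stated use: the ICC is to be obtained for sizing the next trial, and an interval would only display how little it can contribute.

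Third, the article is modest in general terms. It warns about effect sizes, and it calls the trial preliminary when explaining why there is no data monitoring committee. Neither remark mentions the ICC.

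Some stronger readings go too far:
- The 0.27 to 39.5 limits belong to the between-physician mean square, not to the between-physician variance itself.
- A successor about three times too large is possible, but only at an extreme. At true ICC 0.05 the 97.5th percentile of the estimate is 0.29, giving a design effect of 1 + 14 × 0.29 = 5.06 against 1.70.
- One might add that nurse-to-nurse and hospital-to-hospital variance cannot be estimated either. The article claims to estimate neither, and it never states how many nurse navigators there are, so this contradicts nothing in it.

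**Conclusion.** The point holds in a limited form. The design cannot deliver an ICC fit to size the next trial, and the within-cluster argument does not cover the component that is missing. The 2 and 56 degrees of freedom follow from the article alone. Over assumed true ICCs from 0.01 to 0.20, the estimate is zero or negative in 57% down to 19% of trials, and the upper 95% limit is never below 0.75, so the conclusion does not hang on the assumed value.

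The 12%, 22% and 41% shortfalls depend on the assumed ICC, on 15 patients per physician in the successor, and on a zero estimate being used uncritically. A binary outcome, dropout and covariate adjustment were not modelled; they would generally make the ICC less precise.

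This trial's conduct, size, feasibility outcomes and arm comparison are untouched. The text should be corrected, but the defect does not threaten the trial itself.

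**What to change.** In Proposed sample size, restrict the precision claim to the within-physician variance (56 df), and say that the between-physician variance (2 df) is not usefully estimated.

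In Statistical analyses, Primary outcome measures, report the ICC descriptively with its 95% interval. Name the pilot's inputs to the next trial as the patient-level variance, the within-patient covariance, the control-arm rate of blood pressure control, and retention. State that the future trial will be sized over a justified range of external ICCs and not on the pilot's point estimate.

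The cost is wording only. No patient, visit, procedure or budget item changes; the plan gives up an output that four physicians cannot supply.

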### Follow-up phase

Subjects in both arms of the study will be followed up for 6 months after the initial 3-month trial. During the follow-up period, subjects will attend clinics monthly where their physicians will assess them clinically. At months 3, 6 and 9 post enrollment patients and providers will undergo assessments on methodological parameters and consumer responses, clinic BP measurements, medication adherence, health literacy on stroke and HTN as well as self-determination theory constructs such as Autonomous Self-regulation and Competence Scales. Physicians in both groups will also undergo assessment on adherence to BP management protocols (Fig. 1 and Table 1).

**Table 1 Tab1:** Study outcome measures

Outcomes	Psychometrics (internal consistency [α], test-retest reliability [r]) NOTE A^a^	Time points
Primary outcomes		
Feasibility: methodological parameters and consumer responses	Recruitment and retention rates; Self-report: Patient/Provider Satisfaction Scale (.82–.96, test-retest (1 week) .98) [74, 75], fidelity checklists: patient level (e.g., connection; BP uploads via phone; opening of messages/educational information and provider level (e.g., delivery of provider summaries; phone alerts)	Baseline, 3, 6, 9 months
Clinic: BP	Clinic-based BP	
Feedback and refinement	Focus groups	Providers and IG: 9 months
Secondary outcomes		
Medication adherence Physician adherence	Medication Possession Ratio (MPR); Morisky Medication Adherence Scale (α = .76–.83, r = .64) [76, 77], provider guideline adherence: timely med changes (date of script changes following BP feedback (bi-monthly PINGS reports/clinic BPs)	Baseline, 3, 6, 9 months
Self-determination theory constructs	Autonomous Self-Regulation (α = .81–.84, r = .38) [78], Competence Scale (α = .88–.95, r = .32–.46) [51, 52, 78].	
Potential moderators/mediators		
Demographics	Age, education level, income	Baseline
HTN/stroke knowledge, health literacy, anthropometrics	Self-report: HTN/stroke knowledge (.70) [54, 55], health literacy (r = .74, .82) [78–80], Height/ weight/girth	Baseline, 3, 6, 9 months
Medication adherence factors	Side effects, adverse events	As reported, and 3, 6, 9 months

^a^Basic psychometric property analyses (e.g., internal consistency, test-retest reliability) will be conducted during first 3 months on scales, which have not been used with Ghanaian stroke patients

*BP* blood pressure, *HTN* hypertension, *IG* Intervention Group

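### Intermediate BP readings for endpoint imputation are deferred to a future trial, although both arms already attend clinic monthly in months 3 to 9 and those readings could be captured now

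*Protocol article*

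**What the plan says.** All references are to the protocol article.

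- **Statistical analyses, Primary outcome measures: model.** The time points are fixed: "Group and time (baseline, 3, 6 and 9 months) will be fixed effects". The mixed model is also credited with coping with incomplete data: "GLMM allow for missing data, measurement at different times and take into account the effect of clustering".
- **Same section: imputation.** "Multiple imputation methods will be used for missing end-of-study outcomes". The variables that enter the imputation model are not named.
- **Same section: trigger.** The condition is "If more than 10 % of data are missing", and the response is "we will add an intermediate evaluation point in a future RCT to provide more data for use in endpoint imputation". Selective and differential dropout is called an important issue.
- **Follow-up phase: duration and visits.** "Subjects in both arms of the study will be followed up for 6 months after the initial 3-month trial", and "During the follow-up period, subjects will attend clinics monthly where their physicians will assess them clinically". Clinic BP is listed as a study assessment at months 3, 6 and 9.
- **Table 1.** The time points for the primary outcomes, which include clinic BP, read "Baseline, 3, 6, 9 months".
- **The intervention, Patient level.** This section refers to a standard clinic visit at 3 months, which fits awkwardly with monthly clinics.

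**The concern.** The authors accept that readings between the planned points would help to impute the endpoint, but leave them to the next trial. Their own schedule already provides four contacts per patient, at months 4, 5, 7 and 8, in both arms. The article does not say that BP from these contacts is kept as study data.

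Take a patient seen at month 8 who misses month 9. The latest scheduled study BP is then three months old, although a clinic assessment one month old exists. If BP had been rising since month 6 and that rise is linked to the missed visit, the month-8 reading would show it and the month-6 reading would not. What is at stake is how credible missing-at-random is for month 9 and, to a lesser degree, the width of the interval, with 30 patients per arm.

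The choice has to be made before data collection. An analysis plan can choose its imputation predictors later, but it cannot use readings that were never captured.

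**Working it through.** **Inputs from the article.** There are 60 patients, 30 per arm (4 physicians × 15 = 60). Study BP is taken at months 0, 3, 6 and 9. Monthly clinics between months 3 and 9 add months 4, 5, 7 and 8. The trigger is 10% missing, which is 6 of 60 patients at one visit. The article gives no standard deviation, within-patient correlation or expected dropout, so there is no figure of its own to reproduce here.

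**Assumed inputs.** Three within-patient correlation structures for systolic BP, chosen to span a range:

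- A: constant correlation 0.5.
- B: mixed, 0.3 + 0.4 × 0.8^lag, with lag in months. The values do not approach 1 at short lag, so this allows for measurement error.
- C: pure decay, 0.5^(lag/3), with no measurement error.

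**Step 1: how well a missing month-9 value is predicted.** R² = c′S⁻¹c, where S is the correlation matrix of the observed visits and c their correlation with month 9.

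- For A with k visits this reduces to k·ρ²/(1 + (k−1)ρ). With k = 3: 3 × 0.25/2 = 0.375. With k = 7: 7 × 0.25/4 = 0.4375.
- For C only the latest visit counts. Month 6: 0.5² = 0.25. Month 8: (0.5^(1/3))² = 0.5^(2/3) = 0.63.
- B is solved numerically.

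| Structure | Months 0, 3, 6 | Adding 4, 5, 7, 8 | Adding month 8 only |
|---|---|---|---|
| A | 0.375 | 0.438 | 0.400 |
| B | 0.296 | 0.454 | 0.433 |
| C | 0.250 | 0.630 | 0.630 |

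The last column shows that the single most recent reading supplies most of the gain in B and all of it in C. In A it supplies less than half.

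**Step 2: precision of the month-9 arm contrast.** With missing fraction d, the variance inflation is approximately 1 + d/(1−d) × (1−R²). At d = 0.10, d/(1−d) = 0.111:

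- A: 1 + 0.111 × 0.625 = 1.069, against 1 + 0.111 × 0.5625 = 1.063. SE ratio √(1.0625/1.0694) = 0.997, a fall of 0.3%.
- B: 1.078 against 1.061. SE ratio 0.992, a fall of 0.8%.
- C: 1.083 against 1.041. SE ratio 0.980, a fall of 2.0%.

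The same formula at higher missingness:

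| Missing | A | B | C |
|---|---|---|---|
| 10% | 0.3% | 0.8% | 2.0% |
| 20% | 0.7% | 1.7% | 4.1% |
| 30% | 1.1% | 2.6% | 6.4% |

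The approximation ignores variance between physicians. With two physicians per arm, auxiliary readings do nothing for that component, so these falls are upper limits within each structure.

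**Step 3: less favourable attendance.** Steps 1 and 2 assume that every visit before month 9 was attended. If the last visit was month 7, R² with the monthly readings is 0.43 (A), 0.37 (B) and 0.40 (C), against the same 0.375, 0.296 and 0.25 without them. If the last visit was month 5, R² goes from 0.33 to 0.40 (A), from 0.19 to 0.27 (B) and from 0.06 to 0.16 (C). A patient who stops attending right after a quarterly visit gains nothing.

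**The case against.** The strongest reply is that imputation predictors belong in an analysis plan, which is not shown, and that the sentence about a future trial is a conditional design lesson, natural in a pilot. Both points are right. A reader might infer that a missing month-9 value will be imputed from month 6, or that interim readings are barred. The article says neither. What remains is the data-collection schedule, which this document does state and which limits any later analysis plan.

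Other stronger readings also fail:

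- A reader might take month 6 to be multiply imputed as well. The text names only end-of-study outcomes, most naturally month 9. Other gaps are left to the mixed model.
- A reader might say that the extra visits have no use at all in the plan. Table 1 bases physician adherence partly on prescription changes after clinic BPs, and does not restrict these to the quarterly points. BP at months 4, 5, 7 and 8 is likely to be taken. Whether it is recorded as study data is not stated.
- A reader might see a contradiction between monthly clinics and a deferred evaluation point. A routine clinic visit is not a study evaluation, so there is none.

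Two further objections stand and limit the point. Patients who leave care miss the monthly visits too. And the gain in precision is very small at the plan's own 10% trigger.

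**Conclusion.** The point holds as a minor, low-cost improvement. The schedule provides sparser data for imputing a missing month-9 BP than visits already planned in both arms could supply.

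Under the assumed correlations, the rise in R² is 0.06 with constant correlation and 0.38 with pure decay. The second is optimistic for single clinic readings. The effect on the standard error is nearly negligible at 10% missing and still modest at 30%, so precision alone would not justify the change. The better reason is bias: a reading closer to the missed visit makes missing-at-random easier to defend, for intermittent missingness and for dropout between quarterly points only.

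This rests on the monthly clinics taking place as the follow-up section describes, and on BP being measured there, which is likely but not stated.

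**What to change.** 1. In Follow-up phase and Table 1, state that the routine clinic BP from the months 4, 5, 7 and 8 visits is recorded in both arms as auxiliary data, with no added standardised measurement session.
2. In Statistical analyses, Primary outcome measures, allow these readings in the imputation model for month 9. With about 30 patients per arm, the most recent reading before the missing visit, or a summary, is preferable to four separate predictors.
3. Keep months 3, 6 and 9 as the only outcome time points after baseline.
4. Do not use home readings for this. Only the intervention arm is lent the device, and it is returned after the 3-month trial.
5. Reconcile the standard 3-month clinic visit in The intervention, Patient level, with the monthly clinics in Follow-up phase, since the value of the change depends on which visits occur.

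**Cost.** One BP entry at each of four visits already scheduled, at most 4 × 60 = 240 entries under double data entry, and a sentence in the analysis section. The readings will be less standardised and taken by treating physicians. That is tolerable for auxiliary use, but would not be for an outcome.
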